|                                                     | 
Hypothesis: The intervention of a patient-oriented navigation model is feasible in terms of its acceptance, need and practicability in everyday care. To this end, we conduct a comprehensive process evaluation. Primary quantitative feasibility endpoints are the following criteria:
 
 
• 70% of intervention participants take part in the initial in-person interview with the navigator.
 
 
AND
 
 
• Less than 40% of intervention participants drop out of the intervention before the end of the 1-year period (excluding medical or logistical reasons).
 
 
In the case of successfully demonstrated feasibility, the efficacy of the intervention will be tested in relation to one of the patient-reported outcomes studied (e.g., health-related quality of life) as an additional primary outcome. (Authors' comment: defined to outcome 'satisfaction with care' in study registration prior to recruitment start)
 
Secondary endpoints of the study are health-related quality of life, satisfaction with care, health literacy, utilization of care, inpatient hospitalization, mortality and cost-effectiveness.
 
These will be collected from participants in the RCTs as well as participants in the cohort (patients who do not want a navigation intervention) at the same assessment time points.
 |

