|  | 
investigate the feasibility of the navigation model.
 
The navigators have weekly team meetings for mutual support and information exchange. These meetings are accompanied by participant observation by a researcher. In addition, expert interviews with the navigators will be conducted as well as guideline-based interviews with study participants to capture how the navigators support study participants and how this is experienced by study participants and navigators.
 
This serves the purpose of process evaluation as well as the identification of possible needs for change in the navigation model.
 
Other data collection methods
 
a. Data collection RCT
 
Questionnaire Assessments:
 
To examine the effectiveness of the intervention, both groups will receive a baseline assessment on the day of study enrollment (if this is not feasible in individual cases, it may be conducted in the period up to 4 weeks after study inclusion). Follow-up interviews will take place 4 months, 7 months and 13 months after inclusion. (Amendment from August 2021 and January 2022: Vital status of patients is accessed from the registration office prior to follow-up and after study completion to identify lost-to-follow-up participants)
 
Questionnaires can be answered in writing by the study participant or with the help of caregivers or study staff if needed.
 
Secondary data analysis
 
The AOK Nordost provides pseudonymized routine data for all participants of the RCT who are insured with the AOK Nordost. These data contain information on individual treatment and care data, frequency of utilization of health care services, and data on associated costs. The
 |

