|                                                                                                                                                                                                                                                             | 
2. lung cancer
 
A total of 195 lung cancer patients and, if applicable, caregivers (male/female/diverse, age <math>\geq 18</math> years) will be included in the overall study.
 
These will be divided among the study parts as follows:
 
a. RCT
120 lung cancer patients (and caregivers, if applicable).
 
b. Cohort study
75 lung cancer patients
 
c. Qualitative study
Study participants from RCT and cohort study
(in addition, 3 study nurses/navigators (male/female/diverse) aged 18 years and older)
 
d. Secondary data analysis
Approx. 43 lung cancer patients from RCT (depending on the actual AOK-insured proportion in the RCT)
                                                                                                                            |
| 
13. Biometric planning with indication of the statistical methodology, including justification of the number of cases. Indication of the statistician (if advice is given by the Institute of Biometry of the Charité, a signature must be included)
 | 
Biometric Planning:
 
Biometric calculations were calculated based on the two defined primary feasibility outcomes for determining feasibility. These are as follows:
 
"The intervention is feasible if:
 
(1) At least 70% of patients* in the intervention arm participated in at least one initial face-to-face navigator session.
 
AND
 
(2) The dropout rate of the intervention arm of the RCT is less than 40% (here, dropouts are defined as study participants who drop out of the intervention for reasons other than those that physically prevent the patient*/caregivers from participating. E.g., move out of catchment area, deterioration in general health, long-term hospitalization, move to nursing home or hospice, death).
 
Explanations in the individual study sections:
 |

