|  | 
1. Stroke
 
a. RCT
 
For the duration of the recruitment period, we expect a population of about 1850 stroke patients at the three planned recruitment sites (1100 patients at Charité Universitätsmedizin Berlin stroke units at the sites Mitte and Virchow Klinikum, 750 patients at Asklepios Fachklinikum Brandenburg (Amendment from August 2021: Changed to Klinik Hennigsdorf due to change of cooperating physician)) based on data from previous years. We assume that 70% of these patients can be approached by the study personnel for participation in the study. Of the patients approached, we expect a recruitment rate (depending on recruitment site) of 30-50%. Based on these assumptions, we expect 460 stroke patients (and their caregivers) to participate. Based on the feasibility criteria defined above, the statistical planning is as follows: If 460 stroke patients are included in the study, and 230 (50%) of the patients* are randomized to the intervention arm, we assume that at least 95% (n=219) will still have survived to receive patient navigation at 4 weeks. If 166 (75.8%) or more of these 219 patients* receive the initial navigation session, the first feasibility criterion is met, as the 95% confidence interval of this proportion will not be less than 70% (95%CI: 70.1%-81.5%). We additionally assume that of these 230 patients (intervention arm), 85% (n=196) survived after one year. If of these 196 patients, 65 (33.2%) or less are "lost-to-follow-up", the second feasibility criterion will be met, as the 95% confidence interval of this proportion will be less than 40% (95% CI: 26.6%-39.8%).
 
The feasibility of the study is considered successful if both criteria are achieved.
 
In case of successfully demonstrated feasibility, we additionally test the efficacy of the intervention in the study at the two-sided significance level <math>\alpha=0.05</math> using
 |

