|  | 
have survived to receive patient navigation at 4 weeks. If 46 (80%) or more of these 57 patients* receive the initial navigation session, the first feasibility criterion is met, as the 95% confidence interval of this proportion will not be less than 70% (95%CI: 70.5%-90.9%). We additionally assume that of these 57 patients (intervention arm), 75% (n=43) survived after one year. If of these 43 patients, 11 (25.6%) or less are lost-to-follow-up, the second feasibility criterion will be met, as the 95% confidence interval of this proportion will be less than 40% (95% CI: 12.5%-38.6%). The feasibility of the study is considered successful if both criteria are achieved.
 
Analogous to the stroke study, if feasibility is successfully demonstrated, the efficacy of the intervention with respect to a selected patient-reported outcome (e.g., health-related quality of life (Authors' comment: defined to outcome 'satisfaction with care' in study registration prior to recruitment start)) is additionally tested as a primary question at the two-sided significance level of <math>\alpha = 0.05</math> (hierarchical testing). If feasibility cannot be demonstrated, all other outcomes will be analyzed secondarily in an exploratory manner.
 
In addition to the analyses of primary outcomes described at the outset, additional feasibility criteria will be evaluated descriptively/exploratively as secondary outcomes and patient-reported outcomes will be compared between intervention arms in univariate analyses and multiple regression models. Exploratory subgroup analyses will be conducted to examine differences in feasibility and effectiveness related to predefined comparators.
 
b. Cohort Study
We expect the cohort study to have a participation rate of 30% of approached
 |

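### Feasibility criterion 2 is defined as non-excused dropout from navigation in the intervention arm, but its pass rule counts loss to follow-up among assumed one-year survivors

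*Protocol*

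**What the plan says.** Item 2 (aims, hypotheses and endpoints) sets criterion 2 as: "Less than 40% of intervention participants drop out of the intervention before the end of the 1-year period (excluding medical or logistical reasons"). Item 13 (biometric planning) restates it as "The dropout rate of the intervention arm of the RCT is less than 40" per cent and limits the event to "study participants who drop out of the intervention for reasons other than those that physically prevent the patient*/caregivers from participating". Its examples of excused reasons are moving out of the catchment area, deterioration in general health, long-term hospitalisation, a move to a nursing home or hospice, and death.

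The pass rules follow later in item 13. Under Stroke, a. RCT, 85% of the 230 randomised to intervention (n=196) are assumed alive at one year: "If of these 196 patients, 65 (33.2%) or less are" lost to follow-up, the criterion is met. Under Lung cancer, a. RCT, 75% of the 57 assumed alive at four weeks (n=43) are assumed alive at one year: "If of these 43 patients, 11 (25.6%) or less are lost-to-follow-up, the second feasibility criterion will be met". The 230 and the 57 carry the same label, intervention arm. In both diseases a pass requires the upper 95% confidence limit to lie below 40%.

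The only other use of lost to follow-up is in item 8, in the amendment note on the questionnaire assessments: "Vital status of patients is accessed from the registration office prior to follow-up and after study completion to identify lost-to-follow-up participants".

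**The concern.** The definition and the pass rule should describe the same event on the same base. Here the definition concerns leaving navigation, with a list of excused reasons, in the intervention arm. The rule concerns being lost to follow-up, in those alive at one year. Navigation is documented by the navigator, while the questionnaires at 4, 7 and 13 months are a separate activity. A participant can leave one and stay in the other.

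The base raises three separate problems:

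- Restricting to survivors removes deaths but none of the other excused reasons. The text does not say whether a survivor who left for one of those reasons is a non-event, a failure, or outside the base.
- A participant who gives up navigation for a non-excused reason and later dies is in neither the numerator nor the denominator.
- The survivor base is built differently in the two diseases.

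Both criteria must be met for feasibility, and feasibility opens the confirmatory efficacy test. Two analysts following this text could therefore disagree on the primary conclusion, and on whether efficacy is confirmatory or exploratory.

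**Working it through.** **Inputs (Protocol, item 13).** Stroke: 230 randomised to intervention, 196 alive at one year, cut-off 65. Lung cancer: 60 randomised, 57 alive at four weeks, 43 alive at one year, cut-off 11. Limit 40%.

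**Formula.** The protocol does not name its interval. The Wald form, upper limit = p + 1.96·√(p(1−p)/n) with p = x/n, reproduces its figures and is used throughout.

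**Step 1: the plan's own figures.**
- Lung: 11/43 = 25.6%, interval 12.5% to 38.6%, as stated. 12/43 has upper limit 41.3%, so 11 is the right cut-off for n=43.
- Stroke: 65/196 = 33.2%, interval 26.6% to 39.8%, as stated. 66/196 has upper limit 40.3%, so 65 is right for n=196.

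The arithmetic is sound. The question is what is counted, and on which base.

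**Step 2: the base named in the definition (whole arm).** Largest count that passes:
- Lung: 17/60 = 28.3%, upper limit 39.7%; 18/60 gives 41.6%.
- Stroke: 77/230 = 33.5%, upper limit 39.6%; 78/230 gives 40.03%.

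A lung arm with 12 to 17 non-excused dropouts, all among the 43 survivors, would pass on the defined base and fail the stated rule. Here the stated rule is stricter.

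**Step 3: excused non-fatal leavers removed from the base.** The protocol gives no rate, so take the smallest number that matters.

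| Excused leavers removed | Lung | Upper limit | Stroke | Upper limit |
|---|---|---|---|---|
| 0 | 11/43 | 38.6% | 65/196 | 39.8% |
| 1 | 11/42 | 39.5% | 65/195 | 39.95% |
| 2 | 11/41 | 40.4% | 65/194 | 40.1% |

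Two such participants turn a pass into a fail in either disease. On this handling the stated rule is more lenient.

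**Step 4: the same leavers counted literally as lost to follow-up.** If e of the 43 survivors left for excused reasons and were lost, only 11 − e non-excused dropouts are tolerated: 11 at e=0, 3 at e=8. The stated rule is then stricter again.

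**Step 5: non-excused dropouts who later die.** Restore d of them to numerator and denominator. With d=1, lung becomes (11+1)/(43+1) = 12/44 = 27.3%, upper limit 40.4%. Stroke becomes (65+1)/(196+1) = 66/197 = 33.5%, upper limit 40.1%. At the stated cut-offs, one such participant is enough to fail.

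**Step 6: the two constructions exchanged.** Lung survivors built as in stroke: 0.75 × 60 = 45, cut-off 12/45 (26.7%, upper limit 39.6%). Stroke survivors built as in lung cancer: 0.95 × 230 = 218.5, taken as 219 in the plan; 0.85 × 219 = 186.15, so 186, cut-off 61/186 (32.8%, upper limit 39.5%). The cut-off depends on which construction is meant.

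**The case against.** The best defence is that both pass-rule paragraphs refer back to the feasibility criteria defined above them and conclude that the second criterion is met. Lost to follow-up may then be loose shorthand for the defined dropout, and the survivor base a partial attempt to remove excused cases. The item 8 wording comes from a later amendment about vital status and is weak evidence of what the planning text meant. Nothing says that criterion 2 will be scored from missing questionnaires. This is plausible and weakens the charge that a different event is tested. It does not explain why the base is survivors when the definition names the arm, why the two diseases start from different groups, or what happens to dropouts who later die.

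It is also fair that 43 and 196 are planning figures and the final interval will use observed numbers. The cut-offs will move; the mismatch will remain.

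A reader might infer that the two descriptions of excused reasons conflict. "excluding medical or logistical reasons" in item 2 can be read as a summary of the item 13 list, which is itself introduced as examples. A single list would be tidier, but no contradiction is shown.

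**Conclusion.** The point stands as a mismatch between a primary decision rule and its own definition. The base is clearly different; the event is different on its wording, though possibly only through loose terminology. The stated cut-offs have almost no slack: two excused non-fatal leavers taken out of the base, or one later-dying dropout put back, reverses a pass at the margin in either disease. In the other direction, the full-arm base would accept up to 17/60 and 77/230. These results assume the Wald interval and the plan's survival assumptions.

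A reader might infer that the error favours a positive verdict, most of all in lung cancer. The documents do not support that. On the full arm the same counts give only 65/230 = 28.3% and 11/60 = 18.3%, and a literal reading counts excused survivors who are lost as failures. A stroke dropout rate above 40% can be produced by assuming that 20% of survivors (39 of 196) left for excused reasons, giving 65/157 = 41.4%. That rate is not in the protocol, and the protocol does not state a base restricted to those able to continue. No net direction is claimed.

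**What to change.** In both pass-rule paragraphs of item 13:

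1. Replace lost to follow-up by the item 13 event: dropout from navigation for a non-excused reason, taken from the navigator documentation.
2. State one denominator rule for both diseases, built from the same starting group. It should say how every excused exit is handled, not only death, and keep non-excused dropouts who later die in both numerator and denominator.
3. Use the item 13 list of excused reasons wherever the criterion appears, including item 2.
4. Recompute the cut-offs on that base.

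The cost is an amendment to wording. The protocol already requires detailed documentation by the navigator; the sponsor should confirm that the date of and reason for leaving are recorded. The cut-offs will change, and if excused leavers are removed from the base the interval becomes slightly wider. A Kaplan-Meier estimate of dropout with censoring at excused exit could be added as a sensitivity analysis, but it is optional and its absence is not part of the error.

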| 29. Information on the suitability of the trial site, in particular on the adequacy of the resources and facilities available there, as well as on the personnel available to conduct the clinical trial and on experience in conducting similar trials | 
The multiprofessional team of scientists (physicians, epidemiologists, anthropologists, psychologists, health scientists) at the Institute of Public Health has many years of comprehensive expertise and competence in planning, conducting and evaluating epidemiological and qualitative studies. Research focuses on cardiovascular and cancer diseases in the context of decision-making processes, health-related quality of life and patient-centered health services research. The institutions involved in the study also have extensive and long-standing experience in planning and implementing research projects.
                                                                                           |
| 30. Agreement on access of the investigator/principal investigator to the data and the principles of publication.                                                                                                                                       | 
The principal investigator has full access to the collected data. Publication of the study results in national and international peer review journals and in the form of presentations at congresses is planned. No
                                                                                                                                                                                                                                                                                                                                                                                                                                                                                                      |

|                                                                                                                                                                                                                |                                                                                                                     |
|----------------------------------------------------------------------------------------------------------------------------------------------------------------------------------------------------------------|---------------------------------------------------------------------------------------------------------------------|
| 
- Publications in a form that does not allow any conclusion on the person.
                                                                                                                              | 
conclusions can be drawn about individuals when presenting the results.
                                      |
| 
31. Information on the funding of the study: source of funding (name and location) and amount of funding in €.
 
- If applicable, indication of the cost center for the ILV accounting of the fee.
 | 
Federal Ministry of Education and Research
[Address and funding amount deleted for PLOS One publication]
 |
